### 2.8. Criteria for discontinuing the intervention

Sever adverse reactions; Any other disease which affects the efficacy of duloxetine, and determination of Adverse events; Patient is deemed unsuitable for continuing to take duloxetine by the researchers; Subjects withdraw informed consent form; Patients are reluctant to continue their treatment because of poor efficacy; and Lost to follow up.

The reasons for discontinuation and withdrawal would be recorded on the case report form. Subjects who signed informed consent but did not accept the intervention will be replaced. Subjects who signed informed consent, accept the intervention and subsequently withdraw will or may be not replaced.

### 2.9. Lost to follow-up

Participant stops scheduled study follow-up; participant fails to complete study-prescribed procedures; and loss the connection with participant.

### 2.10. Outcomes measures

#### 2.10.1. Primary outcome.

The differential expression of miRNAs between CAPS groups and healthy control groups at baseline.The changes in abdominal pain scores before and after duloxetine treatment in patients with CAPS and their relationship with changes in miRNA.

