**Discussion::**

Findings of study will provide the reliable basis for diagnosis and the predictor of duloxetine efficacy of CAPS. Importantly, findings grant patients a chance to benefit from treatment.

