## 1. Introduction

According to Rome IV criteria, centrally mediated abdominal pain syndrome (CAPS) is characterized by continuous, nearly continuous, or frequently recurrent abdominal pain that is often severe and only rarely related to gut function. CAPS is associated with loss of function across several life domains, including work, intimacy, social/leisure and must be present for at least 6 months before diagnosis.^[1]^

The prevalence of CAPS ranges from 0.5% to 2.1% which is lower than other functional gastrointestinal diseases, such as irritable bowel syndrome (IBS) and functional dyspepsia.^[2]^ However, it is worth note that CAPS has a relatively serious impact on daily life among functional gastrointestinal diseases. Chronic and recurrent pain was the main reason why people visits to gastroenterology outpatient clinic repeatedly.^[3]^ Most of them take numerous unnecessary examinations, receive negative results. Heavy socioeconomic costs include utilization of medical resources and unemployment due to illness.^[4]^ However, the diagnosis of CAPS remains difficult. At present, based on ROME IV criteria, diagnosis of CAPS mainly depends on symptoms, duration and which is an exclusionary diagnosis. It is essential to find a specific and sensitive biomarkers to make a precise and rapid CAPS diagnosis.

Previous studies demonstrated that CAPS resulted from central sensitization with disinhibition of pain signals rather than increased peripheral afferent excitability.^[5]^ Psychological factors will influence human pain perception and down-regulate pain inhibition. Published literacy demonstrated that antidepressants and psychological therapy were potential therapy approaches. Duloxetine is a new SNRIs, mainly inhibits the serotonin and norepinephrine reuptake simultaneously.^[6]^ Current evidence demonstrated that Duloxetine can improve CAPS patients’ frequency of abdominal pain and anxiety.^[7]^ A cohort study of 103 patients found that 53% of patients (n = 10/19, *P* = .007) responded using 1 centrally acting neuromodulator, and effectiveness of duloxetine in CAPS group was 71%.^[8]^ Despite duloxetine seemed to be the most potent single agent neuromodulator, a clutch of patients get unsatisfactory effect. Unfortunately, there is currently a lack of means to predict therapeutic efficacy of duloxetine.

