### 2.3. Study purpose

To evaluate the differential expression of miRNAs in patients with CAPS and healthy controls, to provide new biomarkers for diagnosis of CAPS.To explore the association between the changes of miRNAs and the efficacy of duloxetine treatment at week 4, 12, 24 and 36 in patients with CAPS.

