### 2.4. Studying settings and recruitment

This study is now conducted at Ruijin Hospital from October 1, 2022 to December 31, 2023. We decide to recruit CAPS patients from the inpatient and outpatient of departments of gastroenterology. Meanwhile, the healthy controls will be recruited from the individuals who visit the digestive endoscopy center for routine checkups of gastroscopy and colonoscopy. All participants who experienced physicians will be screened for enrollment eligibility. Diseases will also be diagnosed by experienced gastroenterologists. To enhance participants compliance, they will make appointment for next visit when outpatient clinical visits and will be reminded via telephone or message.

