### 2.5. Eligibility criteria

#### 2.5.1. Inclusion criteria.

All CAPS patients must meet all of the following criteria: age at 18 to 85; meet the Rome IV diagnostic criteria; a signed and dated informed consent form; and commit to comply with study process and align with implementing the whole study process

All healthy controls must meet all of the following criteria: age at 18 to 85; no abdominal pain and other gastrointestinal symptoms; no organic lesions at gastroenterological endoscopy in latest 6 months; a signed and dated informed consent form; and commit to comply with study process and align with implementing the whole study process.

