#### 2.12.2. Data analysis.

Statistical Package for the Social Sciences for Mac book air, version 26 will be used for data analysis. For descriptive statistics, we use proportions for categorical variables, mean ± SD for normal continuous data, median for non-normally continuous data. K-S tests will be used for the normality test. Descriptive statistic is used to describe the demographic characteristics and laboratory test results. Whole data of primary and secondary outcomes are repeated measure and continuous data. X2 test is used for comparison at different time points and intergroup differences in term of baseline data. If the difference is detected statistically significant, post hoc multiple pairwise comparison will be performed. The association of blood biomarkers, plasma concentration, genotype and clinical efficacy, medication adherence will be assessed by Spearman correlation analysis. *P* < 0.05 is considered statistically significant.

We use intention to treat and per protocol to deal with missing values, outlier values, lost follow-up and non-adherence respectively.

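### A significant miRNA difference from symptom-free controls cannot support the diagnostic conclusion that the article announces for CAPS

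*Protocol article*

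**What the plan says.** - **Need.** The Introduction describes CAPS as a diagnosis reached by exclusion and states: "It is essential to find a specific and sensitive biomarkers to make a precise and rapid CAPS diagnosis".
- **Aim.** Section 2.3 compares miRNA expression in CAPS patients and healthy controls "to provide new biomarkers for diagnosis of CAPS".
- **Outcome.** The first primary outcome in section 2.10.1 is "The differential expression of miRNAs between CAPS groups and healthy control groups at baseline".
- **Criterion.** Section 2.12.2 says that P "< 0.05 is considered statistically significant".
- **Comparator.** Section 2.4 recruits controls from "individuals who visit the digestive endoscopy center for routine checkups of gastroscopy and colonoscopy". Section 2.5.1 requires "no abdominal pain and other gastrointestinal symptoms" and "no organic lesions at gastroenterological endoscopy in latest 6 months".
- **Conclusion.** The Discussion part of the abstract says: "Findings of study will provide the reliable basis for diagnosis and the predictor of duloxetine efficacy of CAPS". The closing paragraph of section 3 repeats this a little more softly, saying that the study helps to provide such a basis.

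Other places are more cautious. Section 2.1 speaks of exploring miRNAs, section 2.2 hypothesises only that expression differs, and the first paragraph of section 3 says that an miRNA may in future become a potential diagnostic marker.

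**The concern.** The stated outcome and the announced conclusion answer different questions. A group comparison asks whether two distributions differ at all. A diagnostic claim asks how well a measured value sorts individuals, and in which people. With 215 per group, a difference far too small to classify anyone can be statistically significant.

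The comparator adds a second gap. By the article's own account, CAPS is diagnosed by excluding other causes of abdominal pain. People with no pain and a clean endoscopy are not those in whom the diagnosis is in doubt. The study could therefore meet its first primary outcome, report the conclusion as worded, and leave the clinical question open.

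**Working it through.** **1. The plan's own figure.** Section 2.12.1 gives 172 patients and 20% loss: 172 / (1 − 0.20) = 215, which matches. With 1:1 allocation there are 215 controls. The 172 itself cannot be re-derived, because the article states no effect size and no test.

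**2. Smallest observed difference that reaches P < 0.05.** Assumptions of this check, not of the article: a two-sample t-test, one miRNA, normal values, equal SDs. (Section 2.12.2 names a chi-square test for baseline group differences, so the t-test is a substitution.)

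Critical d = t(0.975, 2n − 2) × √(2/n)

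- n = 215 per group: 1.966 × √(2/215) = 0.190
- n = 172 per group: d = 0.212

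The outcome is measured at baseline, so 215 is the more natural figure. The 172 shows the effect of losing 20% of both groups.

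**3. What that difference means for discrimination.**

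- AUC = Φ(d/√2)
- Sensitivity at 90% specificity = 1 − Φ(1.2816 − d)
- Sensitivity = specificity at the midpoint cut-off = Φ(d/2)

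| n per group | d | AUC | Sensitivity at 90% specificity | Sensitivity = specificity at midpoint |
|---|---|---|---|---|
| 215 | 0.190 | 0.553 | 13.8% | 53.8% |
| 172 | 0.212 | 0.560 | 14.2% | 54.2% |

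An AUC of 0.50 is chance. At 90% specificity, a useless marker has 10% sensitivity.

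**4. This is not only a borderline case.** A true AUC of 0.60 corresponds to d = √2 × Φ⁻¹(0.60) = 0.358. It would be significant with 96% power at 215 per group and 91% at 172. Its sensitivity and specificity at the midpoint cut-off are 57%.

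**5. Could the planned sample support an accuracy measure?** Hanley-McNeil variance with n per group:

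SE² = [A(1 − A) + (n − 1)(u − A²) + (n − 1)(v − A²)] / n², with u = A/(2 − A) and v = 2A²/(1 + A)

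For A = 0.70 and n = 215: u = 0.538, v = 0.576, SE = 0.0251, so the 95% CI is 0.70 ± 0.049 = 0.651 to 0.749. For A = 0.80 it is 0.758 to 0.842. The sample is large enough.

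**6. The comparator.** No arithmetic applies. Sections 2.1, 2.4 and 2.5.1 define two groups: CAPS patients and symptom-free people. No group with IBS, functional dyspepsia or organic abdominal pain is enrolled. A sensitivity, specificity or AUC from these two groups describes CAPS versus healthy and nothing else. The Introduction and section 3 themselves report altered miRNAs in IBS. The IBS miRNAs they name are not among the 11 from the pilot, so overlap is not shown. But the design cannot rule it out.

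**The case against.** The strongest reply is that this is a condensed article without its analysis plan. ROC curves, cut-offs and validation are commonly left to such a plan, and section 2.12.2 does not claim to be exhaustive. That stands. A reader might infer that the group comparison is the only diagnostic analysis planned, or that only means will be compared. The documents support neither: silence in a summary is not a decision, and no section says that means are the quantity tested.

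The exploratory wording noted above also counts. For the hypothesis in section 2.2, differential expression against healthy people is a coherent first-stage endpoint, and the sentence on specific and sensitive markers describes a need in the field rather than an outcome of this study.

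The AUC of 0.55 is what the criterion permits, not what is expected. Several miRNAs combined might discriminate better, and nothing says that a barely significant miRNA would be declared diagnostic.

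It is also tempting to read 172 as powered for d = 0.39 between groups. That is one of several readings. At two-sided 0.05 and 95% power, 172 also fits d = 0.55 (86 per group), d = 0.275 (paired) or a correlation of 0.27.

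None of this removes the mismatch. An unseen plan could add an ROC analysis. It would not alter the primary outcome, the comparator or the conclusion published here.

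**Conclusion.** The concern holds as a mismatch between the outcome and comparator on one side and the announced conclusion on the other. Under the t-test, single-miRNA, equal-variance normal assumptions, 215 per group can yield P < 0.05 with an AUC of about 0.55 and 14% sensitivity at 90% specificity. Those figures depend on the assumptions. The point about the comparator does not: against healthy controls, no accuracy figure, however high, shows that CAPS can be told from IBS or organic pain. The differential-expression result itself remains valid. What lacks support is the diagnostic conclusion in the abstract and at the end of section 3.

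**What to change.** 1. Base any diagnostic statement on discrimination: AUC with its 95% CI, and sensitivity at a specificity fixed in advance. If miRNAs are selected or combined (the 11 pilot miRNAs are an obvious candidate set), validate internally, with the selection repeated inside the validation. The choice of model, validation scheme and any minimum AUC is for the sponsor to state beforehand.
2. Reword the conclusion in the abstract and in the closing paragraph of section 3 as first-stage evidence on CAPS versus healthy people, in line with the cautious wording already in section 3. Separation from other causes of abdominal pain would remain a question for a study with symptomatic comparators.

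The cost is a little more analysis of data already to be collected, and a more modest claim. No extra participants or visits are needed.

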## 2. Methods and analysis

### 2.1. Study design

This study is a prospective cohort study conducted in China (ChiCTR2200064371). Our study aims to explore serum miRNAs as a diagnostic biomarker and a predictor of efficacy of duloxetine for patients with CAPS.

Blood samples will be taken from participants who visited our hospital. A total of 215 CAPS patients and 215 healthy controls will be enrolled from the inpatient and outpatient departments of gastroenterology and the digestive endoscopy center respectively.

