### 2.2. Study hypothesis

We hypothesized that: there is differential expression of miRNAs between CAPS group and healthy control group; duloxetine would improve abdominal pain; and miRNAs may be associated with the prognosis of patients with CAPS after duloxetine treatment.

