**Figure 2. F2:**
[figure not shown]
Study procedure. ADR = adverse drug reaction, BP = blood pressure, Cmax = maximum serum concentration, GAD7 = Generalized Anxiety Disorder7, HAMA = Hamilton anxiety scale, HAMD = Hamilton depression scale, HR = heart rate, NRS = numerical rating scale, PHQ9 = patient health questionaires 9, PRS = pain relief scale, PSQI = Pittsburgh sleep quality index, QoL = quality of life, SF36 = short form 36.

After the initial visit, every patient starts to take duloxetine under the instruction of gastroenterologist. The initial dose is 30 mg qd. After 1 week, if tolerated, increase dose to 60 mg qd, or 30 mg qd continued. In the duration of therapy, altering dose of duloxetine based on pain relief scale (PRS) score. We suggest adding 30 mg every 2 weeks, however, the total dose should not exceed 120 mg qd.

During the treatment period, patients need to have 3 outpatient visits as follow-up including 1 month (visit 2), 3 month (visit 3) and 6 months (visit 4) after the treatmet, respectively. Patients will be required to complete the same questionnaires as at the initial visit and 2 additional questionnaires, including PRS and Morisky questionnaire. Biochemical indicators, Maximum serum concentration of duloxetine, blood miRNA will be tested in the laboratory of Ruijin Hospital. Adverse drug reaction will also be recorded.

After 24-week treatment period, there is a further 12-week outpatient post-treatment follow-up period. At the terminal visit (visit 5), patients will be required to complete all the rating scales except Morisky questionnaire. Adverse drug reaction will also be recorded. Micro RNA, genotype and blood routine will be tested again.

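### The aim is a predictor of duloxetine efficacy, but the primary outcome relates pain change to miRNA change with no time order, in patients who all take duloxetine

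*Protocol article*

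**What the plan says.** **The aim.** Section 2.1 of the protocol article sets out to "explore serum miRNAs as a diagnostic biomarker and a predictor of efficacy of duloxetine for patients with CAPS". The Introduction gives the motive: "there is currently a lack of means to predict therapeutic efficacy of duloxetine". The Abstract's Discussion paragraph and the closing paragraph of section 3 both announce a predictor of duloxetine efficacy as what the study will deliver.

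**The endpoint.** The second primary outcome in section 2.10.1 is "The changes in abdominal pain scores before and after duloxetine treatment in patients with CAPS and their relationship with changes in miRNA". The Abstract and the secondary outcome (2.10.2) have the same form. The second purpose in 2.3 is "To explore the association between the changes of miRNAs and the efficacy of duloxetine treatment at week 4, 12, 24 and 36".

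**The hypotheses.** Section 2.2 says "duloxetine would improve abdominal pain; and miRNAs may be associated with the prognosis of patients with CAPS after duloxetine treatment".

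**The analysis.** Section 2.12.2 plans Spearman correlation between blood biomarkers (with plasma concentration and genotype) and clinical efficacy. It does not say which miRNA time point enters.

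**The groups.** Section 2.7 says "After the initial visit, every patient starts to take duloxetine under the instruction of gastroenterologist". The Abstract has healthy controls giving blood at the initial visit only. Table 1 schedules miRNA and NRS at all five visits (months 0, 1, 3, 6 and 9).

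**The concern.** There are two gaps between claim and design.

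**Time order.** A predictor of benefit has to be known before the benefit. The stated outcome uses change in miRNA and does not say that this change is measured before the pain outcome. If both changes run over the same interval, the miRNA change is known only when the pain result is known. It may then be a monitoring marker or an effect of pain relief. The quantity available before the first dose, miRNA at visit 1, is measured in every patient but is not the predictor in any stated outcome.

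**Attribution.** No CAPS group goes without duloxetine, and the healthy controls contribute no change over time. A fall in pain therefore mixes drug effect with placebo response, regression to the mean and natural course. For the same reason, a marker of prognosis cannot be told from a marker of benefit from the drug.

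At stake is the interpretation of a positive primary result. It could be reported as a predictor of efficacy when baseline miRNA predicts nothing and the drug contributes nothing.

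**Working it through.** **1. The plan's own figure.** Section 2.12.1 gives 172 patients and 20% loss: 172 / (1 − 0.20) = 215, which reproduces the stated group size. No effect size, SD or test is given behind the 172, so I use it only as the number of evaluable patients, with the stated two-sided α = 0.05 and power 0.95.

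**2. Claim against endpoint.**

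| Place | What it commits to |
|---|---|
| 2.1, Abstract (Discussion), section 3 (close) | predictor of duloxetine efficacy |
| 2.10.1, 2.10.2, Abstract | change in score related to change in miRNA |
| 2.3, second purpose | changes of miRNA related to efficacy at weeks 4, 12, 24 and 36 |
| 2.2, third hypothesis | miRNA associated with prognosis after treatment |
| 2.12.2 | Spearman correlation of biomarkers with efficacy, time point not given |

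Every passage that defines the miRNA-response endpoint or purpose uses change in miRNA. Only 2.2 and 2.12.2 leave room for a baseline level, and neither is an outcome definition.

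**3. How much untreated drift would pass as an effect.** Assume a paired t-test of NRS before and after (the article does not name this test). The standardised change detectable with 95% power is approximately

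(1.960 + 1.645) / √172 = 3.605 / 13.115 = 0.275,

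or 0.276 with the exact t distribution. In NRS points this is 0.276 × SD of change. The article gives no SD, so I show a range:

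| Assumed SD of change | Drift detected with 95% power | Chance that a drift of 0.25 is significant | Chance that a drift of 0.5 is significant |
|---|---|---|---|
| 1.5 | 0.41 | 58% | 99% |
| 2.0 | 0.55 | 37% | 90% |
| 2.5 | 0.69 | 26% | 74% |

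**4. Can change against change be positive when baseline miRNA is uninformative?** Illustrative simulation, n = 172, 4,000 runs, all parameters assumed:
- Pain is a stable trait (SD 1) plus independent visit-level variation (SD 1), with a natural fall of 0.5 and no drug effect. The SD of change is √2 = 1.41, so the standardised drift is 0.5 / 1.41 = 0.35.
- Baseline miRNA is unrelated to pain.
- The miRNA change is 0.4 × the standardised pain change plus noise of SD 0.9, a correlation of about 0.4.

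| Test at two-sided 0.05 | Significant | Mean Spearman rho |
|---|---|---|
| miRNA change against pain change | 99.98% | 0.39 |
| Baseline miRNA against pain change | 5.0% | 0.00 |
| Before-after change in pain | 99.4% | n/a |

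The first row follows almost directly from the assumed correlation of 0.4, so it is not an estimate of how often this would happen. The contrast between the first two rows is the result: same-interval co-variation says nothing about whether the pre-treatment level predicts.

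**The case against.** **The time order is open, not wrong.** A reader might infer that the stated predictor has no lead time at any visit. The documents do not support that. Section 2.10.1 names no interval, and 2.3 does not tie each miRNA change to pain at the same visit. Change from week 0 to 4 against pain at week 24 would fit the wording and precede the outcome by 20 weeks. This stands: the defect is that the order is not fixed.

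**The second question may still be answerable.** A reader might infer that the trial as written cannot address prediction at all. That also goes too far. The Spearman plan in 2.12.2 is not restricted to change scores, 2.2 speaks only of association with prognosis, and a fuller plan could fix the time point. This stands in part: a baseline analysis is possible, but it would not be the analysis of the primary outcome as defined in this article.

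**A single treated cohort is legitimate.** The design is openly a prospective cohort with exploratory aims, and the absence of an untreated CAPS group is not an error in itself. This stands. The criticism is of the claims: "duloxetine would improve abdominal pain" and predictor of efficacy assert more than such a cohort can show.

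**The drift figures are assumed.** No NRS SD, correlation or untreated course is given. A drift set equal to the detectable change is significant 95% of the time by construction. This stands, so the figures are shown only as a range.

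**Conclusion.** The point holds as a mismatch between claim and endpoint. The aim and intended conclusion are a predictor of duloxetine efficacy. The primary outcome relates pain change to miRNA change, does not require miRNA to come first, and does not use the visit-1 level. It could be positive when that level carries no information. Separately, with every CAPS patient treated and controls sampled once, neither an effect of duloxetine on pain nor a marker specific to drug benefit can be shown; association with outcome during treatment can.

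The textual part rests on no assumption. The size does: with 172 evaluable patients, a paired t-test and an SD of change between 1.5 and 2.5 NRS points, an untreated drift of about 0.4 to 0.7 points would be significant with 95% power. A drift of 0.25 points would be significant 26% to 58% of the time. These figures illustrate sensitivity to drift; they do not estimate the drift that will occur, and no single false-positive rate can be drawn from the article.

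**What to change.** 1. Restate the second primary association in 2.10.1 as visit-1 miRNA with NRS at one prespecified later visit (for example week 24), by linear regression or a mixed model adjusted for baseline NRS. Align the Abstract, 2.3 and 2.12.2.
2. Keep change in miRNA against change in pain as an exploratory analysis, and state the interval for each change.
3. In 2.1, 2.2, the Abstract and section 3, limit the hypotheses and conclusions to within-patient change during treatment and prognostic association in duloxetine-treated patients. The third hypothesis in 2.2 is already close to this.

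No new visit or assay is needed: Table 1 already schedules miRNA and NRS at every visit. The cost is a change to the outcome wording, a matching registry update and a more modest claim. A claim specific to duloxetine would still need a concurrent CAPS comparison group, which this design does not have.
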